#### **i. Unexpected or serious adverse events**

The Principal Investigator will use continuous vigilance to identify and report adverse events within 72 hours of identification of the event to all approving HRECs and relevant Research Governance Officers.

## **11. DATA ANALYSIS**

### **a. Quantitative**

#### **Statistical methods**

[name], epidemiologist and Chief Investigator on the project and has led the development of the statistical plan.

#### **Primary outcomes**

Directed Acyclic Graphs (DAGs) are being used to determine variables that need to be collected to adjust for potential confounding within statistical models. DAGs enable the conceptualisation of causal pathways. A DAG has been done for each primary outcome.

Generalized linear mixed effects models (GLMMs) with compound symmetric (exchangeable) correlation structure will be used to account for within health care centre (cluster) correlation; logit or log link will be used for binary outcomes such as prevalence resulting in mixed effect logistic regression, while log link will be used for count outcomes resulting in mixed effects negative binomial regression. GLMMs are a missing data method only assuming missing at random – MAR (instead of the more stringent MCAR – missing

completely at random). Effect measures will also be presented through calculation of number needed to treat and its associated 95% confidence interval. Analysis after the 12-month intervention follow-up is planned, spending  $\alpha=0.005$ .

In addition, a descriptive pre-post analysis of survey results due to participating in the PSN alone in the first six months will be calculated using appropriate parametric or non-parametric tests. These analyses will occur after each collection timepoint.

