## Sample

**Training program:** We will aim to recruit two participants per service. In discussions about the project with services, most services have more eligible staff. There must be at minimum one participant but is no upper limit to the number of participants from each service. The sample size will include an estimated uptake of (n=40) and accounted for drop-out rate of 50% of the AHW/P. Therefore, (n=20) participants would need to complete the training program.

**Interviews enablers and barriers:** We will aim to recruit between 3 and 15 participants of the training program given time and feasibility.

**Systems assessment:** The number of chronic disease staff who participate in the system assessment focus group will vary by service, depending on how large the team is and the number who consent to participate. There is no upper or lower limit to the number of staff who participate in the focus group; it depends on the staff willing to participate and who are available on the day.

**Medical record review:** Participants will not be recruited; Medical records (existing data) of people with diabetes in each participating service who meet the inclusion criteria will be audited retrospectively. The number of people with diabetes who receive care at each service enrolled in the study and meet the study inclusion criteria will vary. Prevalence of self-reported diabetes varies between 8 and 23% according to the 2018-19 ABS National Health Survey. It is therefore expected that between 8 and 23% of clients at each enrolled service will meet the eligibility criteria.

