## Randomisation

Randomisation will occur at the service level. Enrolled health services will be randomised into Group A and Group B. Randomisation and allocation will be undertaken after six months of providing PSN for all enrolled health service sites and prior to commencement of the training program. All enrolled health service sites will be listed, and a statistician will be responsible for randomizing the health service sites into cluster one (Group A participants) or cluster two (Group B participants) using a block size through a computer program for randomisation.

For the intervention assignment; a cluster crossover randomised trial will be employed in this study, as all participants receive the same intervention based on random service site allocation. Participants in the study sites will know which group they have been allocated after completing six months of the PSN, and before commencing the E-Learning module for group A. The project research team will not be blinded to group A or B allocation, only people analyzing the results will be masked/blinded.

**Peer Support Network (months 1-17):** Only AHW/Ps will participate in the PSN. AHW/P participants from both Group A and Group B will participate in the PSN for the entire duration of the study. The PSN will commence and convene for 6 months prior to Group A doing the e-learning modules and the OS. The PSN will run online via Teams, once a month, for 1.5 to 2 hours duration, and will be facilitated by a credentialed diabetes educator (DNE) who is a research team member.

As this is a pragmatic trial, it is understood that AHW/Ps may not be able to attend all PSN sessions due to competing work and/or personal priorities.

The PSN meetings will not be recorded. The PSN Facilitator will record participation in the network.

**E-Learning Modules (10 weeks):** There are 9 self-paced e-Learning modules. Each module takes approximately 1 hour to complete. Ten weeks have been allocated to complete the e-learning modules. All participants will do the e-learning modules. Services will have agreed to allow their staff to use the work computers and internet and to do the modules during work hours. These can also be done from any computer, at any time. The modules can be left and picked up at the same place for convenience during working hours.

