## **Data collection timepoints for the primary outcomes**

For the entire study there are seven points in time at which data will be collected. These are labelled T0 (baseline), T1 – T6 in Figure 4 and are referred to in the below outline of data collected. Reason for the training program data collection timepoints are as follows:

- T0- Baseline - groups A & B
- T1 - Measure Effect of Peer Support Network - 6 Months Post Baseline Group A & B (Aboriginal Health Workers and Practitioners only).
- T2 – Measure effect of training program (PSN, Online Modules, Onsite Support) on group A - 8.5 Months post-baseline (data collected on both group A & B).
- T3 – Baseline of group B prior to doing the intervention (data collected on both group A & B), 14.5 months post-baseline.
- T4 – Measure effect of training program (PSN, Online Modules, Onsite Support) on group B post group B undertaking the intervention at 17 months from baseline (data collected on both group A & B).
- T5 – Sustainability of effect of training program on group A 23 months post-baseline, and group B 6 months post commencement of intervention.
- T6 - Sustainability of effect of training program on group A 29 months post-baseline, and group B 12 months post commencement of intervention.

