| Demographics                    | Characteristics of individuals, their work experience and the site they are employed by                                                             | Research team developed                               | 11                  | T0, T5, T6                                                   | RedCap                                                               | All participants                                                                                   |
| Primary Outcomes                | Diabetes knowledge                                                                                                                                  | Simplified diabetes knowledge scale                   | 20                  | T0, T1, T2, T3, T4, T5, T6                                   | RedCap                                                               | All participants                                                                                   |
|                                 | Confidence in managing diabetes                                                                                                                     | Diabetes Confidence Survey                            | 15                  | T0, T1, T2, T3, T4, T5, T6                                   | RedCap                                                               | All participants                                                                                   |
|                                 | Attitude relating to diabetes                                                                                                                       | Diabetes Attitude Scale (DAS-3)                       | 25                  | T0, T1, T2, T3, T4, T5, T6                                   | RedCap                                                               | All participants                                                                                   |
|                                 | Diabetes management in practice & skill                                                                                                             | Research team developed                               | 9                   | T0, T1, T2, T3, T4, T5, T6                                   | RedCap                                                               | All participants                                                                                   |

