| Potential confounding variables | Variables that have the potential to reduce bias in statistical models to give a more accurate estimate of cause and effect of the training program | Based on Directed Acyclical Graphs                    | 5                   | Varied                                                       | RedCap (3 variables are collected in demographic and PSN evaluation) | All participants                                                                                   |
| Health Service Characteristics  | Health service characteristics for delivery of evidence based diabetes care                                                                         | Assessment of Chronic Care Scale                      | up to 50            | Once between months 3 and 12 of the study commencement       | Face to face or zoom                                                 | Multi-D team diabetes or chronic disease team within each service                                  |

Table 3: Summary of data collection methods

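### The protocol gives confounding as its basis for adjustment and does not name each outcome's T0 score as a model term, although T0 is collected from all participants before randomisation

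*Protocol*

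**What the plan says.** Protocol section 11.a (Primary outcomes) gives one reason for adjustment: "Directed Acyclic Graphs (DAGs) are being used to determine variables that need to be collected to adjust for potential confounding within statistical models". It adds that a DAG has been done for each primary outcome. The model is a generalised linear mixed model with an exchangeable structure that "will be used to account for within health care centre (cluster) correlation". No fixed effects are listed: not group, period, time, T0 score or any covariate.

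Table 3 (section 10.c) counts five potential confounding variables in a row separate from the primary outcomes. Their source is given as "RedCap (3 variables are collected in demographic and PSN evaluation", and their timing as varied. The same table schedules every primary outcome at "T0, T1, T2, T3, T4, T5, T6" from all participants. The timepoint list in section 10.c has "T0- Baseline - groups A & B".

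On allocation, section 10.b (Randomisation) states: "Randomisation and allocation will be undertaken after six months of providing PSN for all enrolled health service sites". T0 therefore precedes allocation by about six months.

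On size, section 10.a (Sample) states: "The sample size will include an estimated uptake of (n=40) and accounted for drop-out rate of 50% of the AHW/P". It concludes that 20 "participants would need to complete the training program". Section 14.c refers to a potential 17 health services.

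**The concern.** In a comparison of randomised groups, a variable measured before allocation can be associated with group only by chance. Confounding is therefore not the property that makes a covariate useful. What matters is how well it predicts the outcome, and the best predictor is normally the same instrument's earlier score. The protocol collects that score from everyone but names only a confounding rule.

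Three features make it worth naming T0 explicitly.

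- The timepoint list uses the word baseline twice, once for T0 and once for T3 in Group B. T3 comes after randomisation and after Group A's training, so adjustment for baseline would be ambiguous.
- T1 is limited to Aboriginal Health Workers and Practitioners in the timepoint list but assigned to all participants in Table 3. T0 is thus the only pre-randomisation score that both places give for everyone.
- Some DAG variables come from demographic and Peer Support Network surveys, which are also collected after allocation. The stated rule does not require an adjustment variable to be measured before randomisation.

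At stake is precision in a very small trial, and the conditional error from a chance difference in starting scores.

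**Working it through.** **The plan's own figure.** 20 completers / (1 − 0.5) = 40 recruits, which reproduces. No power calculation, effect size, SD, ICC or T0-outcome correlation (rho) is stated, so what follows is illustration.

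**Inputs.**
- From the protocol: 20 completers and 40 recruits (section 10.a); 17 potential services (section 14.c).
- Assumed: services split 8 and 9, all contributing data; continuous score with SD 1; effect 0.8 SD; ICC 0.05; two-sided 5%; rho 0.3, 0.5 or 0.7.

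**Formulas.** With m = N/17 participants per service, the variance of a service mean is V = [1 + (m − 1) × ICC]/m × (1 − rho²). The standard error of the group difference is SE = √[V × (1/8 + 1/9)]. Power comes from a noncentral t with noncentrality 0.8/SE, on 15 df unadjusted or 14 df with T0.

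**Example.** For N = 20 unadjusted, m = 1.176 and V = 1.0088/1.176 = 0.858. Then SE = √(0.858 × 0.2361) = 0.450 and the noncentrality is 0.8/0.450 = 1.78, giving power of 38%.

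| N | Analysis | SE | Noncentrality | Power |
|---|---|---|---|---|
| 20 | unadjusted | 0.450 | 1.78 | 38% |
| 20 | T0, rho 0.3 | 0.429 | 1.86 | 41% |
| 20 | T0, rho 0.5 | 0.390 | 2.05 | 48% |
| 20 | T0, rho 0.7 | 0.321 | 2.49 | 64% |
| 40 | unadjusted | 0.327 | 2.44 | 63% |
| 40 | T0, rho 0.3 | 0.312 | 2.56 | 66% |
| 40 | T0, rho 0.5 | 0.283 | 2.82 | 75% |
| 40 | T0, rho 0.7 | 0.234 | 3.42 | 89% |

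Residual variance falls by rho², that is by 9%, 25% and 49%. At ICC 0.2 the gains at rho 0.5 are similar: 9.5 points with N = 20 and 12 points with N = 40.

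**Simulation check.** Seventeen services were split 9 and 8 and analysed by weighted regression of service means, with 6,000 runs per cell. At rho 0.3, power went from 38.0% to 39.3% (N = 20) and from 62.2% to 63.3% (N = 40). At rho 0.5 it went from 38.2% to 45.6% and from 62.4% to 71.3%. A second simulation, by generalised least squares on individual data, gave 36% to 44% and 60% to 72% at rho 0.5.

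Across the methods the gain is about 1 to 4 points at rho 0.3 and about 7 to 12 points at rho 0.5.

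**At the stated alpha.** The only alpha in the protocol is 0.005, for the analysis after the 12-month follow-up. The first simulation at that level and rho 0.5 gave 10.7% to 14.5% (N = 20) and 24.6% to 31.7% (N = 40).

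**Chance imbalance.** Ignoring clustering, the SD of the T0 difference between groups is √(2/10) = 0.45 SD with 20 participants and √(2/20) = 0.32 SD with 40. The chance of a difference beyond 0.5 SD is 26% and 11% respectively. A difference of 0.5 SD moves an unadjusted estimate by 0.5 × rho, that is by 0.15 to 0.35 SD for rho 0.3 to 0.7.

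**The case against.** A reader might infer that the DAG variables are the only covariates and that T0 is left out of the model. The documents do not support that. Section 11.a lists no fixed effects, so on the same reasoning the treatment group would be missing too. The DAG sentence concerns which variables to collect, and T0 scores are collected anyway as outcomes, so a separate row in Table 3 is expected either way. Covariate lists are commonly left to a statistical analysis plan, which is not shown. Attachment 14, with the variable list, is not shown either.

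T0 may also already be used as a repeated response: outcomes run from T0 to T6, and the de-identification section links each participant's records over time. That route recovers about the same precision, provided group means are set equal at T0 and within-person correlation is modelled. Section 11.a does not rule it out, but it states neither condition and names only correlation within centres.

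Three further objections stand.
- Chance imbalance is not bias. It is part of the sampling variance over repeated randomisations, and it shifts the estimate only conditionally.
- The calculation assumes a continuous score. The protocol names logit and log links for binary outcomes and a log link for counts. In a logistic model, adjustment changes the odds ratio being estimated and need not shorten its interval.
- DAG reasoning remains legitimate for the comparisons that are not randomised contrasts, such as the Peer Support Network pre-post analysis and the later sustainability timepoints, and where dropout is heavy. Demoting the DAG variables to a sensitivity analysis is a debatable trade-off, and this point does not need it.

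What remains is that the protocol states a selection principle that does not lead to the most useful covariate, and it never says how that covariate enters.

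**Conclusion.** The point holds as an unstated term that should be fixed. The protocol gives confounding as its basis for adjustment and does not name the T0 score, although that score is available from both groups before randomisation. It cannot be concluded that T0 is excluded, or that the planned estimate is biased.

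The cost of leaving T0 out cannot be fixed from the documents. Under the illustrative assumptions it is about 1 to 4 points of power at rho 0.3, which is minor, and about 7 to 12 points at rho 0.5, which matters in a trial of this size. These figures rest on a continuous score, an effect of 0.8 SD, 17 contributing services and two-sided 5%. At ICC 0.2 instead of 0.05 the gains at rho 0.5 are much the same.

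**What to change.** In section 11.a, state that each primary Group A versus Group B model includes the participant's own T0 score on the same instrument as a fixed covariate. Equivalently, state that T0 is modelled as a response with equal group means at T0 and with within-person correlation. Name T0 explicitly, so that T3 cannot be read as the baseline. Keep any DAG variables in addition, limited in these comparisons to values measured before randomisation.

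The cost is one degree of freedom per outcome and a simple rule for missing T0 scores. Mean imputation with a missingness indicator would serve for the covariate form; the constrained-baseline form is the alternative. No new data, visits or participants are needed, because T0 records are already linked to later surveys by study ID.

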## **Data collection procedures**

### **Demographics, primary outcomes, potential confounding and peer support network evaluation variables**

At each relevant time point of data collection, each participant will receive an email from the Study Manager with a unique URL link to the RedCap Survey. Each time a survey is sent, participants will have up to 14 days to complete the survey. For incomplete surveys, up to three email prompts and one phone call will be used to remind participants to complete the survey. At each data collection time point survey's will be closed after 14 days.

Demographics are collected three times during the study period and will take 5 minutes to complete. The primary outcomes are collected seven times and in total take up to 35 minutes to complete. The peer support network evaluation questions are collected monthly after each PSN session and take approximately 5 minutes to complete.

Surveys can be programmed to be sent automatically on a given date which can be changed as well as sent manually if required.

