### **b. De-identification**

Data will be collected at several points in time.

**Individual level data – training program participants:** On entry into the study each participant will be allocated a unique ID (URID) within RedCap. The Study Manager will enter enrolled participant details into RedCap including participant first name, surname, date of birth, email address, enrolment date, consent status, consent status and consent form. This will create a participant list and will assign each participant a URID within RedCap, so that their baseline and subsequent evaluations can be linked for the duration of the study. REDCap keeps the URID, and participant name separate to the participant data. The participant data will only include the URID. Only de-identified data will be analysed during the study. Individual data will not become part of any report or publication of the project.

Data collected by semi-structured interviews with AHW/Ps and multidisciplinary health care providers will not be linked to the survey data. This data will be aggregated and thematically analysed. Name or date of birth will not be collected from interview participants.

**Service level data (systems assessment):** Each health service will be given a unique ID by the Study Manager. A linking key that holds the service name and unique service ID will be kept in a separate file location. All service level information will include the unique ID only.

**Quality of care and patient outcomes (medical record review):** The health service will allocate a unique ID to each patient record, and this will be kept by the service. Only de-identified audit data will be provided to the research team (Attachment 14). Should the research team need to clarify anything, they will provide the relevant health service with the unique ID number; the health service will then follow-up the query using the patient record.

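### The primary mixed model names correlation within health centre but no participant-level term, so if visits are analysed together, change contrasts lose power and the missing-at-random claim does not hold

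*Protocol*

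**What the plan says.** Protocol section 11.a (Primary outcomes) gives the model as follows: "Generalized linear mixed effects models (GLMMs) with compound symmetric (exchangeable) correlation structure will be used to account for within health care centre (cluster) correlation". It then adds that "GLMMs are a missing data method only assuming missing at random – MAR", in contrast to the stricter missing-completely-at-random assumption. Neither this section nor any other names a participant random effect or a within-participant covariance.

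The data are longitudinal at the level of the individual:
- Section 10.c, data collection timepoints for the primary outcomes: "For the entire study there are seven points in time at which data will be collected", labelled T0 to T6.
- Section 10.c, data collection procedures: "The primary outcomes are collected seven times and in total take up to 35 minutes to complete".
- Section 11, De-identification: each participant gets a unique ID "so that their baseline and subsequent evaluations can be linked for the duration of the study".

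The number of surveys is seven at most. The timepoint list describes T1 as "6 Months Post Baseline Group A & B (Aboriginal Health Workers and Practitioners only", which leaves six for the other participants, although Table 3 shows all participants at every timepoint.

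On the design, "Randomisation will occur at the service level" (section 10.b). The Sample section aims for two participants per service, with a minimum of one. It expects an uptake of 40 and allows for 50% drop-out among the Aboriginal Health Workers and Practitioners, which leaves 20 to complete the training.

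**The concern.** The design has three levels (visit, participant, service) and the stated model has two. An exchangeable structure at centre level gives every pair of observations in a service the same correlation, whether they come from one person or from two.

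Two things are at stake. First, a change within a person is measured more precisely than this model believes, because the stable part of each person's score cancels from the difference. The model leaves part of that stable variation in its residual and overstates the standard error. Secondly, likelihood inference adjusts for dropout that depends on a person's earlier scores only if the model ties that person's later scores to the earlier ones. Here the tie is no stronger than to a colleague's scores. The protocol nevertheless relies on the model for validity under missing at random, in a small trial that expects heavy loss.

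**Working it through.** **Plan's own figure.** 20 / (1 − 0.5) = 40, as stated. The protocol gives no standard error, SD, intraclass correlation or power that could be reproduced.

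**Inputs.** From the protocol: 40 participants, up to 17 services (section 14.c calls the number potential), seven visits, Group A trained before T2 and Group B before T4. Assumed: total variance 1, service variance 0.05, participant variance 0.3, 0.5 or 0.7, the remainder residual (0.65, 0.45, 0.25), Gaussian outcome, no true effect.

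**Step 1: expected size by algebra.** For a within-participant contrast the true variance is proportional to the residual variance e. A centre-only model pools between-person variation inside services into its residual. With N people, S services and T visits, its residual is approximately e + c·p, where p is the participant variance and c = (N − S)T / [(N − S) + N(T − 1)]. Over T0–T3, c = 23×4 / (23 + 120) = 0.643. The ratio of model to true standard error is √[(e + c·p)/e]:
- p = 0.3: √(0.843/0.65) = 1.14
- p = 0.5: √(0.772/0.45) = 1.31
- p = 0.7: √(0.700/0.25) = 1.67

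**Step 2: simulation without dropout.** Restricted maximum likelihood fits with fixed visit effects, 150–250 replicates per setting. Ratios are model SE to empirical SE.

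| Contrast, centre-only model | p = 0.3 | p = 0.5 | p = 0.7 |
|---|---|---|---|
| Difference-in-differences T0–T3, SE ratio | 1.18 | 1.31 | 1.59 |
| Rejection at nominal 0.05 | 0.024 | 0.020 | 0.008 |
| All seven visits, SE ratio | 1.25 | 1.29 | 1.71 |
| Rejection at nominal 0.05 | 0.008 | 0.020 | 0.000 |
| A versus B at T2–T3 only, SE ratio | 1.01 | 0.97 | 1.00 |

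With a participant intercept added, the ratios for the same contrasts lie between 0.95 and 1.11. At 250 replicates a ratio carries Monte Carlo error of about 1/√500, or 4–5%. A separate simulation (T0–T3, intraclass correlation 0.05, within-person correlation 0.5–0.7) gave ratios of about 1.4–1.5.

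**Step 3: what this costs in power.** For an illustrative effect of 0.5 SD (assumed), approximate power is P(Z > 1.96·r − 0.5/s), where s is the empirical SE from the T0–T3 runs (0.248, 0.212, 0.166) and r is the SE ratio. The centre-only model gives 0.39, 0.42 and 0.45. With a correct standard error (r = 1) power is 0.52, 0.65 and 0.85.

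**Step 4: dropout driven by the participant's own previous score** (roughly 40–50% lost by T6). Bias is in SD units.

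| Quantity | Centre only | With participant intercept |
|---|---|---|
| T0-to-T6 change (p = 0.5, 0.7) | +0.29, +0.33 | +0.02, −0.01 |
| A versus B, dropout alike in both arms | at most 0.013 | at most 0.006 |
| A versus B, dropout starting earlier in Group A (p = 0.3–0.7) | +0.04 to +0.16 | −0.02 to +0.01 |

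For T0-to-T6 change the centre-only model rejected in 18–29% of trials with no true change. The separate simulation, with score-driven dropout in Group A only, biased the treatment contrast by 0.22–0.29 SD, against about 0–0.02 SD with a participant intercept.

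**The case against.** The strongest reply is that the sentence does not say centre correlation is the only correlation modelled. The section lists no fixed effects or visits, mentions a statistical plan, and may leave the random effects to that plan. Each timepoint also has its own stated purpose. If every A-versus-B comparison used one visit, each person would contribute one record and a centre-level term would be adequate. This stands in part: the finding is conditional on visits being analysed together. It does not remove the point. The protocol fixes a structure, the level it applies to and a missing-data property said to follow from it. That property has value only where a person's visits are modelled jointly.

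Three stronger readings are tempting, and the documents do not support them.
- A reader might infer that standard errors for purely post-training comparisons are too small. The ratio is 0.97–1.01 here and 0.95–1.05 in a further simulation. Rejection slightly above 5% reflects a normal critical value with 17 clusters: with t on 15 degrees of freedom it was 3.3–6.5%.
- A reader might infer that any score-related dropout passes into the treatment effect. With dropout alike in both arms it hardly does.
- A reader might take 50% as the survey loss for everyone. The protocol ties it to Aboriginal Health Workers and Practitioners completing the training.

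It is also fair that the simulations are Gaussian, whereas the protocol mentions logit and log links for binary and count outcomes. Those models were not simulated.

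**Conclusion.** The point holds for any primary model that uses more than one visit per person. As written, the model ignores the extra similarity of repeated scores from one person. Standard errors for within-participant change contrasts are then roughly 15–70% too large when there is no dropout. The error is conservative: it costs power and does not create false positives.

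The missing-at-random statement is not true of this model. Change over time is biased by about 0.3 SD from T0 to T6 even when both arms lose people alike, which matters for the sustainability questions at T5 and T6. The A-versus-B contrast is biased by about 0.04–0.3 SD, depending on how far dropout differs between arms. Such a difference is plausible, because Group A does the modules and onsite support while Group B waits.

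The sizes rest on the assumed variance components, 17 services, 40 participants and a Gaussian outcome. The direction follows from the structure of the model.

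**What to change.** In section 11.a, state that any model using more than one visit per person includes random intercepts for service and for participant within service. Attach the missing-at-random statement to that model and drop it as a general property of mixed models.

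No new data are needed, since the linking ID already exists. The cost is one sentence and one extra variance component, which may be weakly separated from the service component where a service has a single participant. A small-sample degrees-of-freedom correction for the limited number of services is worth considering, but it is a separate and optional point.
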